## Abstract

**Background:**

It is a priority to achieve smoking cessation in diabetic smokers, given that this is a group of patients with elevated cardiovascular risk. Furthermore, tobacco has a multiplying effect on micro and macro vascular complications. Smoking abstinence rates increase as the intensity of the intervention, length of the intervention and number and diversity of contacts with the healthcare professional during the intervention increases. However, there are few published studies about smoking cessation in diabetics in primary care, a level of healthcare that plays an essential role in these patients. Therefore, the aim of the present study is to evaluate the effectiveness of an intensive smoking cessation intervention in diabetic patients in primary care.

**Methods/Design:**

Cluster randomized trial, controlled and multicentric. Randomization unit: Primary Care Team. Study population: 546 diabetic smokers older than 14 years of age whose disease is controlled by one of the primary care teams in the study. Outcome Measures: Continuous tobacco abstinence (a person who has not smoked for at least six months and with a CO level of less than 6 ppm measured by a cooximeter) , evolution in the Prochaska and DiClemente's Transtheoretical Model of Change, number of cigarettes/day, length of the visit. Point of assessment: one- year post- inclusion in the study. Intervention: Brief motivational interview for diabetic smokers at the pre-contemplation and contemplation stage, intensive motivational interview with pharmacotherapy for diabetic smokers in the preparation-action stage and reinforcing intevention in the maintenance stage. Statistical Analysis: A descriptive analysis of all variables will be done, as well as a multilevel logistic regression and a Poisson regression. All analyses will be done with an intention to treatment basis and will be fitted for potential confounding factors and variables of clinical importance. Statistical packages: SPSS15, STATA10 y HLM6.

**Discussion:**

The present study will try to describe the profile of a diabetic smoker who receives the most benefit from an intensive intervention in primary care. The results will be useful for primary care professionals in their usual clinical practice.

**Trial Registration:**

Clinical Trials.gov Identifier: NCT00954967

## Background

It is known that tobacco is the principal isolated cause of avoidable morbimortality in developed countries. Half of these deaths are premature, provoking a loss of 5.5 million potential years of life annually, 3.3 million in men and 2.2 million in women [1]. Smoking related diseases are the cause of death in 50% of smokers [2]. The most recent mortality data indicate that tobacco causes 54,233 deaths annually in Spain [3]. In a study about mortality attributable to the active consumption of tobacco in Spain from 1978 to 1992, it was observed that 1 out of every 3 deaths was in a person younger than 65 years of age who had a high life expectancy [3].

The morbimortality observed in diabetics is related to macro and microvascular complications, and tobacco has a multiplying effect on these vascular complications. Furthermore, it has been demonstrated that tobacco consumption is associated with mortality due to isquemic heart disease in diabetic patients [4]. A number of studies have found evidence relating tobacco consumption to the development of nephropathies in type 1 and 2 diabetes mellitus [4]. It has also been shown that the tobacco consumption is a risk factor for the development and progression of diabetic neuropathies [5].

According to recommendations in national and international guidelines, achieving smoking cessation is a priority in diabetic smokers, given that this group has two to four times more cardiovascular risk when compared to the general population [6-8].

In the present study, Prochaska and DiClemente's Transtheoretical Model of Change will be used. This model describes a series of successive stages (precontemplation, contemplation, preparation, action and maintenance) that signal a different type of intervention depending on the person's stage. Despite the discrepency regarding the utility of this model in smoking cessation [9,10], the majority of clinical guidelines in primary care (PC) consider useful because it helps to make decisions regarding treatment. Furthermore, it allows the professional to gauge the evolution of the patient's attitude towards smoking cessation.

Although there are differences between type 1 and type 2 diabetes, previous studies show that the majority of diabetic smokers are in the pre-contempative stage of Prochaska and DiClemente's model. In a study by Ruggiero et al, people that received some type of smoking cessation advice made more progress in the process of smoking cessation [11].

Cooximeters have been used to demonstrate continued smoking abstinence. Consensus documents have recommended this technique, concluding that it is useful in diagnosing and in aiding with the process of smoking cessation [12].

It its known that minimum advice for smoking cessation in the general population achieves a mean 5% smoking cessation in one year [13] while interventions with intensive follow-ups can achieve a mean of 20% smoking cessation [14]. In general, abstinence rates increase with the intensity of the intervention, the time used in the intervention and the number and diversity of contacts with the healthcare professional, including follow-up visits [4,15]. Health interventions in tobacco consumption can be considered to have a low cost in relation to the quality and years of life gained. From a public health point of view, the obtained results possibly constitute the most cost efficient process to improve the health of the population [14,16].

Integrating pharmocological treatments that have been shown to be efficient in meta analyses and systematic revisions (nictone substitutes, Bupropion and Varenicline) has also been shown to be useful [17-19].The efficacy and effectiveness of interventions using recommendations similar to the present study have also been studied in PC, such as the ISTAPS study [20].

Due to the difficulty of an interventon in a population as advised and resistant to change as diabetic smokers [21,12], advancing in the stages of change of Prochaska and DiClemente's model, as well as decreasing the number of cigarettes, are also seen as important in addition to smoking abstinence [21,12].Therefore, they will also be objectives in the current study.

Various studies have shown that the more intense an intervention, the better the results obtained. In Persson et al [22], a Swedish study carried out in 412 diabetic smokers in PC, subjects in the intervention group received smoking cessation advice and were followed by telephone or in group sessions, while subjects in the control group were mailed smoking cessation advice. The one-year abstinence rate was 20% in the intervention group and 7% in the control group. Furthermore, within the intervention group, 40% of those who participated in the group therapy quit smoking, compared to 14% in of those who were followed by telephone. In Canga et al [23], a randomized clinical trial that evaluated the effectiveness of an smoking cessation intervention using intensive follow-up in diabetic smokers, the six-month continued abstience rate was 17% in the intevention group and 2.3% in the control group. In intervention group subjects that did not quit smoking, the number of cigarettes smoked decreased. It was concluded that a structured intervention increases smoking cessation in diabetic smokers.

Another study in diabetic smokers carried out in Minneapolis, Minnesota [24] concluded that programs for diabetes education should include intensive interventions for smoking cessation because they increase the efficacy of advice and do not have a negative effect on the metabolic control of diabetes.

There are only a few studies published about smoking cessation in diabetic smokers in PC, despite the fact that most diabetic patients visit their PC physician various times per year for routine check ups. According to the World Health Organization [25], diabetes control and prevention activities should be based in PC. This suggests that PC is the ideal environment for intensive interventions in smoking cessation in diabetic smokers.

For all of the abovementioned reasons, the effectiveness of an intensive smoking cessation intervention in diabetic smokers in PC, based on the Prochaska and DiClemente Transtheoretical Model of Change and motivational interview techniques, will be evaluated in the present study.

## Hypothesis

The present smoking cessation intervention in diabetic patients in PC, which uses an intensive strategy that is motivational, individualized, structured and adapted accoding to the Prochaska and DiClemente's Transtheoretical Model of Change, will cause a difference in continued abstinence of 12% between patients that receive the intervention versus those who do not. This takes into consideration the fact that smoking cessation in the general population is 5% with minimum advice [13] and 20% with intensive advice [14].

## Objectives

### Principal objective

To evaluate the effectiveness of an intensive intervention to obtain continued smoking abstinence in diabetic patients in PC.

### Secondary objectives

1. To study the effectiveness of an intensive smoking cessation intervention in the evolution of Prochaska and DiClemente's Transtheoretical Model of Change in diabetic patients in PC.

2. To study the effectiveness of an intensive smoking cessation intervention in the evolution of tobacco consumption in diabetic patients in PC.

3. To quantify the time spent on the intensive smoking cessation intervention versus usual clincial practice in PC.

## Methods/Design

### Design

Cluster randomized trial, controlled and multicentric. Randomization unit: Primary Care Team (PCT).

### Setting

43 PCTs from the province of Barcelona that provide health coverage to urban, semirural and rural populations.

### Study population

Type 1 and 2 diabetic smokers older than 14 years of age that receive routine diabetes care in the participating PCT. An active smoker is defined as a patient that responds affirmatively to the following questions: 1. Do you smoke currently? 2. Have you smoked more than 100 cigarettes in your lifetime? 3. Have you smoked any tobacco product in the last seven days? [26,27].

### Exclusion criteria

Patients with communication difficulties (cognitive or sensory deterioration, language barrier); patients that have not had check ups for their diabetes in the PCT for more than one year; patients with terminal illnesses, serious psychologial illnesses, active addictions to other psychoactive substances; patients that are already in the process of quitting smoking; patients that live more than six months outside of the territory assigned to the PCT; and patients who do not consent to participate in the study.

### Withdrawl criteria

Any event that may lead to a situation that discourages the intervention or that may prevent communication with the healthcare professional.

### Sample size calculation

The sample size has been calcuated by multipying the size of a randomized simple design by the design effect. In the simple randomized design, considering an alpha error of 0.05 a beta error of 0.20 in a bilateral contrast, and given that 15% of diabetics are smokers, 124 subjects were needed in each study group in order to determine a difference in continued abstinence of greater than or equal to 12% between study groups. A continued abstinence of 5% was assumed for the non intervention group, and a potential loss of follow-up of 20% was estimated.

Using an intracluster correlation coefficient of 0.05 [28-30], and based on an average of 25 diabetic smokers per PCT, the design effect is 2.2. Therefore, 546 diabetic smokers and 22 PCT were needed. The sample size was calculated using the Granmo 5.2 program for Windows.

### Data Collection

#### Dependent Variables

• Continued abstinence (yes, no) is defined as at least six months without smoking and a CO breath level of <6 ppm, measured by a cooximeter in standard conditions.

• Stage change in Prochaska and DiClemente's Transtheoretical Model of Change (advance, maintained, backwards, relapse).

• Number of cigarettes per day, reported by the patient.

• Total time (in minutes) spent on the intervention.

#### Independent Variables

• Variables related to the patient (information obtained through an individualized interview):

- Administrative: PCT, PC professional, data collection date, patient code.

- Sociodemographics: date of birth, sex, level of education.

- Anthropometric: weight, height.

• Related to diabetes: type, year of diagnosis, type of treatment, presence of complications related to diabetes (peripheral arterial disease, ischemic heart disease, retinopathy, neuropathy, nephopathy).

• Related to associated pathologies: COPD, cerebrovascular accident, isquemic heart disease, hypertension, hypercholesterolemia.

• Variables related to tobacco consumption: age at initiation of habit, number of cigarettes per day, nicotine dependence (Fagerström test), motivation to quit (Richmond test), number of previous attempts to quit for at least 24 hours, smoking cessation treatment with mediciations, maximum time of abstinence, phase of the patient according to Prochaska and DiClemente's model (pre-contemplation, contemplation, preparation-action), tobacco in usual environment (family, partner, friends, coworkers, classmates), perceived grade of harmfulness of tobacco on diabetes, point prevalence abstinence (smoking abstinence at the time of the visit and with a CO level of less than 6 ppm), length of abstinence.

• Variables related to the intervention: attendance of intervention visit, date of intervention visit, date of D day, time spent on intervention visit, medication used for smoking cessation, relapse, reason for relapse, CO level in breath, observations.

• Variables related to the one-year follow-up visit: attendance to follow-up visit, date of follow-up visit, smoking status, number of cigarettes per day, length of abstinence, phase of the patient according to Prochaska and DiClemente's model (pre-contemplation, contemplation, preparation-action), CO level in breath, observations.

• Variables related to the PCT: years the PCT has been operating, assigned population, mean age of assigned population, whether or not it is a teaching center for residents, number of doctors, number of nurses, number of social workers, other specializations, number of centers.

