### Statistical analysis

Data will be analyzed in concordance with the Consort Cluster guide [31], and all analyses will be done on an intention to treat basis. A descriptive analysis and an analysis of baseline comparability between the study groups will be performed for the variables studied. A T-student test or a U Mann Whitey will be used to compare means with two categories, an ANOVA test will be done to compare means with two or more categories, and a Chi- squared test or a Chi -squared tendency test will be done to compare categorical variables. A multilevel logistic regression and a Poisson regression will be done to evaluate the association between each of the dependent variables and the independent variables that have resulted statistically significant in the bivariate analisis. All analisis will be adjusted for potential confounding factors and for variables with clinical relevance. All tests will be done with a 95% bilateral confidence interval. SPSS 15, STATA 10 and HLM6 will be used.

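### The covariate rule sets no limit on team-level variables in a comparison of 22 to 43 randomized teams; with 22, the nominal 5% test may run at about 8–9%

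*Protocol article*

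**What the plan says.** The Independent Variables section of the protocol article lists, for each PCT, "years the PCT has been operating, assigned population, mean age of assigned population, whether or not it is a teaching center for residents". It goes on to the numbers of doctors, nurses and social workers, other specializations, and the number of centers. That makes nine PCT-level variables.

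The Statistical analysis section names unclustered bivariate tests (Student t, Mann-Whitney, ANOVA, chi-squared). It then fits multilevel logistic and Poisson regressions of each outcome on whichever independent variables came out significant in those tests. It adds: "All analisis will be adjusted for potential confounding factors and for variables with clinical relevance". PCT-level variables are neither exempted nor capped.

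Randomization is by center, 1 to 1 (Phase 2). On numbers, the Sample size calculation says "Therefore, 546 diabetic smokers and 22 PCT were needed", while the Setting section gives 43 PCTs. The Discussion says the design effect will be allowed for in all main analyses. The article does not state the estimation method, the reference distribution or the degrees of freedom.

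**The concern.** Because whole PCTs are randomized, the information on the intervention effect is close to one observation per PCT. With 22 PCTs and two arms, 20 degrees of freedom remain to judge between-PCT variation, and every PCT-level covariate takes one of them. If the between-PCT variance is estimated by maximum likelihood, it also shrinks as PCT terms are added, so a normal-theory interval for the group effect becomes too short.

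The screening step makes such terms likelier to enter. A PCT-level variable tested against a patient-level outcome, as if patients were independent, looks significant far more often than 5% of the time.

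At stake are the coverage of the 95% interval and the size of the 5% test for continued abstinence, the principal outcome.

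**Working it through.** **1. The plan's own figures.** Inputs from the Sample size calculation: error rates ("considering an alpha error of 0.05 a beta error of 0.20 in a bilateral contrast"), the target ("in order to determine a difference in continued abstinence of greater than or equal to 12% between study groups"), control rate 5%, and 20% allowed for loss to follow-up. The arcsine formula for 5% against 17% has h = 2·asin√0.17 − 2·asin√0.05 = 0.399. So n = 2(1.96 + 0.842)²/h² = 98.6 per arm, and 98.6/0.80 = 123.3, which matches "124 subjects were needed in each study group". The clustering input, "Using an intracluster correlation coefficient of 0.05", with 25 patients per PCT gives a design effect of 1 + 24 × 0.05 = 2.2. Then 248 × 2.2 = 545.6, or 546 patients, and 545.6/25 = 21.8, or 22 PCTs. The plan's figures are reproduced.

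**2. How many irrelevant PCT variables pass the screen.** I read bivariate significance as association with the outcome. For a test that ignores clustering, the chance of passing a nominal 5% screen is about 2[1 − Φ(1.96/√DE)].
- 22 PCTs × 25, DE 2.2: 0.186 each, so 9 × 0.186 = 1.7 of nine.
- 43 PCTs × 13, DE 1 + 12 × 0.05 = 1.6: 0.121 each, so 9 × 0.121 = 1.1 of nine.

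Simulation gave 1.6 and 1.1.

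**3. Analytic check.** With J PCTs and q PCT covariates, df = J − 2 − q. Using 1.96 with an unbiased variance gives an error rate of P(|t_df| > 1.96). If the variance is the maximum-likelihood one and all variation lies between PCTs, the rate is P(|t_df| > 1.96√(df/J)), which serves as a guide to the upper end.

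| PCTs | q | df | unbiased, z | ML, z |
|---|---|---|---|---|
| 22 | 0 | 20 | 6.4% | 7.6% |
| 22 | 2 | 18 | 6.6% | 9.3% |
| 22 | 9 | 11 | 7.6% | 19.3% |
| 43 | 0 | 41 | 5.7% | 6.3% |
| 43 | 9 | 32 | 5.9% | 10.1% |

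**4. Simulation.** Assumptions: no true effect, ICC 0.05, beta-binomial clustering, equal PCT sizes, abstinence 5% or 11% in both arms, PCT variables unrelated to outcome, random-intercept logistic model fitted by maximum likelihood, z test. Ranges cover several sets of runs of 800 to 6,000 trials per cell.

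| PCT covariates in the model | 22 PCTs | 43 PCTs |
|---|---|---|
| none | 6.1–8.5% | 4.7–6.8% |
| nine candidates, screened | 7.1–9.5% | 5.4–7.6% |
| two, fixed | 8.5–8.7% | 5.5–7.4% |
| five, fixed | 11.4–11.6% | 6.8–8.3% |
| all nine | 14.2–16.3% | 8.1–10.3% |

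In the largest runs at 22 PCTs (about 6,000 trials), the rates were 6.7–7.4% with none, 8.0–8.2% screened and 14.4–15.2% with all nine.

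**5. Other ICCs** (all nine entered, 5% abstinence, ICC 0.01, 0.02, 0.10). 22 PCTs: 7.4%, 9.7%, 15.8%. 43 PCTs: 6.3%, 6.4%, 10.3%. About 2% of fits at 22 PCTs with nine covariates (ICC 0.05, 5% abstinence) failed and were dropped; at ICC 0.10 it was about 10%.

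**6. After the change.** In the logistic model at 22 PCTs with a t reference, the rate is 4.6–6.3% with no PCT covariate and about 6.5% with two. With all nine it stays at about 9–11%. A PCT-level analysis of cluster proportions on t with J − 2 − q df gives 4.6–5.3% with zero to two covariates.

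**The case against.** The strongest reply is that the Independent Variables section is a data-collection list (it also holds the patient code and observations), and the plan never says that all nine PCT variables will be modelled. Under the stated screening, one or two would enter by chance. That adds only about one point at 22 PCTs (8.0–8.2% against 6.7–7.4%), and at 43 PCTs the difference is within simulation error. About 7% at 22 PCTs comes purely from the assumed z reference, and a condensed article may leave estimation and degrees of freedom to the full plan. A PCT-level analysis with the right t reference holds about 5% even with nine covariates. The Discussion also promises to allow for the design effect.

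Most of this stands and limits the size of the point. It does not remove it. The selection rule is printed, not omitted, and it chooses PCT-level terms with tests unsuited to them. The clause on clinical relevance can admit several more. Allowing for the design effect is no rescue in itself, since the simulated models already carry a PCT random intercept.

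Two stronger readings do not hold. A reader might infer that the error rate is three times nominal. That needs all nine terms, only 22 PCTs, an ICC near 0.05 or higher, and a maximum-likelihood z test, and the article states neither the first nor the last; with 43 PCTs even the worst case is about twice. A reader might also infer that the many patient-level variables push the odds ratio away from 1. With 27 irrelevant covariates screened as stated, about 1.3 entered and the median odds ratio did not move visibly (3.98 to 4.00 with 436 patients, 4.05 to 4.00 with 546). A shift to 4.4–4.5 appeared only when all 27 were forced in.

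**Conclusion.** The point holds in a limited form. The printed rule admits PCT-level covariates without a limit into a comparison that rests on 22 to 43 PCTs, and picks them with tests that ignore clustering. Given ICC 0.05 and a maximum-likelihood fit with a normal reference, the 5% test runs at about 8–9% with 22 PCTs and 5–8% with 43 under the stated screening. The 14–16% (22 PCTs) and 8–10% (43 PCTs) figures are worst cases with all nine in the model. Part of the excess at 22 PCTs, up to about 7%, is not caused by the PCT variables. The interval can be too narrow; the documents do not show that it must be. The simulation covers only PCT variables unrelated to outcome. The change is worth making because it is cheap and, with recruitment still under way according to Phase 3, can be made before the one-year outcomes are analysed.

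**What to change.** In the Statistical analysis section, for the intervention-effect model:

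- Replace selection by bivariate significance with a short list of baseline covariates named in advance. It should contain no PCT-level variable, or at most one or two. Report the remaining PCT variables descriptively by arm.
- Test the group effect on a t distribution with (PCTs − 2 − PCT covariates) degrees of freedom, or by permuting PCTs.

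Limiting the PCT terms is the essential part, since the t reference alone does not repair a maximum-likelihood model carrying all nine.

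Cost: wording only, plus slightly wider intervals. With no PCT covariate the critical value is 2.09 at 22 PCTs (about 6% wider than with 1.96) and 2.02 at 43 (about 3% wider). Chance imbalance in the other PCT features would be described and not adjusted for.
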